**Fig. 3 Fig3:**
[figure not shown]
Schedule of enrolment, intervention, and assessments (SPIRIT) figure

### Adverse events

Any adverse events will be reported by the patients and outcome assessors, including severe pain, local infection, or unbearable tingling during treatment, and will be recorded during the trial. If any serious adverse events or uncontrolled hypertension occur, they will be immediately reported to the primary investigator and the patient will be withdrawn from the trial. There is no anticipated harm and compensation for trial participation.

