### Interventions

The physician will provide lifestyle education to all patients for 12 weeks, which mainly includes sending relevant antihypertensive information to patients every week and holding health lectures every month. The content of the information includes influence of lifestyle on hypertension control, especially the strength of dietary health, and the importance of moderate physical exercise, maintaining normal weight and quitting smoking. In addition, we will establish a communication group to answer questions raised by patients during the intervention. If patients were on antihypertensive medication, they were instructed to continue this medication but to abstain from changing the type or dosage of drugs.

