### Outcomes

#### Primary outcome

The primary outcome of the study is the change in mean SBP between baseline and 12 weeks after treatment. BP will be measured and recorded by using an electronic sphygmomanometer (HEM-7136, Omron Corporation, Kyoto, Japan) in both groups. Patients were asked to rest quietly for at least 5 min before taking blood pressure measurements of the upper arm in the sitting position, with the upper arm at heart level [23]. Blood pressure in both upper arms should be measured at the first test; the side with the higher blood pressure reading will be selected. At subsequent detection time points, the measurement will be repeated 3 times every 5 min; the average value of the last 2 readings will be taken as the mean BP [24].

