#### Secondary outcomes

The mean SBP will be evaluated at weeks 24 and 36 after randomization. The mean DBP, body mass index (BMI), International Sports Activity Questionnaire (IPAQ), and Short Form (SF-12) will be evaluated at baseline, 12 weeks, 24 weeks, and 36 weeks. The DBP measurement method is consistent with SBP. BMI is weight (kg) divided by the square of height [25, 26]. The IPAQ questionnaire includes the frequency, intensity, timing, and type of exercise [27], which will be divided into three levels of physical activity levels by metabolic equivalent (MET). The SF-12 is a questionnaire to evaluate general health outcomes including psychological and physical domains [28, 29].

The schedule of enrolment, intervention, and assessments is shown in Fig. 3.

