### Statistical analysis

Statistical analysis will be conducted by SPSS version 23.0 (IBM SPSS Statistics, NY, USA). Intention-to-treat analysis (ITT) will be applied to all cases randomly assigned to each group [31]. We will try our best to collect the data for the patients who quit or lost the visit in this trial. The last observation carried forward (LOCF) will be used for missing data. There is no interim analysis or additional analysis in this trial. The level of significance will be established at *α* < 0.05 with a two-sided test. Patients’ baseline characteristics will be described for the two groups. Continuously distributed variables will be described using mean ± standard deviation (M ± SD) or median and quartile intervals. Discrete variables will be described by frequencies and percentages. For the primary outcome, the change in SBP between baseline and 12 weeks after treatment will be calculated and the difference of the change in SBP between the two groups will be tested using Student’s *t* test or the Wilcoxon rank sum test. For secondary outcomes, Student’s *t* test, chi-squared test, Fisher’s exact test, or the Wilcoxon rank sum test will be used to test the difference of the outcomes including the DBP, BMI, IPAQ, and SF-12, between groups according to the distribution of variables.

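### Uncontrolled hypertension ends trial participation, not just treatment, so LOCF may replace SBP readings that are missing because SBP is high (minor; cheap to improve)

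*Protocol article*

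**What the plan says.** All references are to the protocol article.

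- **Adverse events.** "If any serious adverse events or uncontrolled hypertension occur, they will be immediately reported to the primary investigator and the patient will be withdrawn". The sentence goes on to name what is left, namely the whole study and not only the treatment: "the patient will be withdrawn from the trial". The rule covers both arms. The text gives no blood pressure threshold for uncontrolled hypertension and no follow-up after withdrawal.
- **Primary outcome.** "The primary outcome of the study is the change in mean SBP between baseline and 12 weeks after treatment".
- **Secondary outcomes.** "The mean SBP will be evaluated at weeks 24 and 36 after randomization". The text describes no trial reading between baseline and week 12. The schedule figure is not shown, so interim readings cannot be ruled out.
- **Statistical analysis.** On the analysis population: "Intention-to-treat analysis (ITT) will be applied to all cases randomly assigned to each group". On gaps in the data: "The last observation carried forward (LOCF) will be used for missing data". On patients who leave: "We will try our best to collect the data for the patients who quit or lost the visit in this trial".
- **Interventions.** Of patients already on antihypertensive drugs: "they were instructed to continue this medication but to abstain from changing the type or dosage of drugs".

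**The concern.** The variable that triggers withdrawal is also the outcome. A patient leaves because blood pressure is high, later SBP readings stop, and LOCF supplies a substitute. That substitute is either out of date (baseline) or selected for being high (the reading that triggered withdrawal). If TEAS lowers SBP, more controls than TEAS patients will trigger the rule, so the substitution need not cancel between arms.

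For a control patient there is no device to stop. Withdrawal then ends little besides the lifestyle education and the measurement. An analysis plan cannot repair this later, because it cannot analyse readings that were never taken.

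Serious adverse events fall under the same rule and also cost data, but their link to SBP is weaker and no bias is claimed for them.

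**Working it through.** The plan gives no figure to reproduce: the sample size is a pilot convention without an effect size or SD. The check has two parts.

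**1. What LOCF carries, by time of detection**

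| Uncontrolled hypertension found | Week 12 | Weeks 24 and 36 |
|---|---|---|
| (1) before week 12, outside a trial reading | baseline carried, change = 0 | baseline carried |
| (2) before week 12, at a trial reading | that reading carried | that reading carried |
| (3) at the week-12 visit | observed, unaffected | high week-12 value carried |
| (4) at week 24 | observed | week 36 filled with the week-24 value |

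Weeks 24 and 36 are exposed in more cases than week 12.

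**2. Size**

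From the document: 30 patients per arm; eligibility up to SBP 159. Everything else is assumed:
- baseline mean 148, SD 5.5
- control week-12 mean 143 or 146; SD of later readings 12 or 15
- correlation of baseline with later readings 0.4; among later readings ρ = 0.5 or 0.7
- mid-period mean halfway between 148 and the week-12 mean
- true effect -5 mmHg, persisting to week 24; every event detected
- thresholds T = 160, 170, 180 (160 is least favourable, just above the eligibility limit)

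This makes 8 scenarios per threshold. φ is the normal density and P the probability of exceeding T.

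*Standard error.* SD of change = √(5.5² + SD² − 2×0.4×5.5×SD) = 11.0 (SD 12) or 13.8 (SD 15). SE = SD of change × √(2/30), about 2.8 to 3.6 mmHg.

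*Week 24, case (3).* LOCF raises an arm's mean by (1−ρ)×SD×φ(z), with z = (T − week-12 mean)/SD.
- Largest at 160 (ρ 0.5, SD 15, control mean 146). Control: z = 0.933, 0.5×15×0.258 = 1.94. TEAS: z = 1.267, 0.5×15×0.179 = 1.34. Difference -0.6, so LOCF shows about -5.6.
- Smallest at 160 (ρ 0.7, SD 12, control mean 143). Control: z = 1.417, 0.3×12×0.146 = 0.53. TEAS: z = 1.833, 0.3×12×0.074 = 0.27. Difference -0.26, so LOCF shows -5.26.

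*Week 12, case (1).* The shift in an arm is (148 − week-12 mean)×P + (0.4×5.5 − ρ×SD)×φ(z), with z taken from the mid-period mean. Largest at 160 (ρ 0.7, SD 15, control mean 146):
- Control: z = 0.867, 2×0.193 − 8.3×0.274 = -1.89.
- TEAS: z = 1.033, 7×0.151 − 8.3×0.234 = -0.89.
- Difference +1.0, so LOCF shows -4.0.

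Simulation with 2 million patients per arm agrees. Ranges over the 8 scenarios:

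| LOCF estimate (truth -5) | 160 | 170 | 180 |
|---|---|---|---|
| Week 24, case (3) | -5.60 to -5.26 | -5.37 to -5.07 | -5.13 to -5.01 |
| Week 12, case (1) | -4.61 to -4.00 | -4.91 to -4.57 | -4.99 to -4.87 |
| Week 12, case (2) | -5.16 to -4.84 | -5.14 to -5.04 | -5.07 to -5.01 |

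With half the events detected, week 12 in case (1) at 160 is -4.80 to -4.50. With equal arms and equal detection the bias is zero.

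*The alternative: keep measuring, with rescue of R mmHg.* An arm's mean falls by R×P. In the largest week-24 case at 160, P = 0.175 (control) and 0.103 (TEAS). With R = 15 the estimate moves by 15×0.073 = +1.09, to -3.91. Over all scenarios with R = 8 or 15 it is -4.64 to -3.91, which is 0.4 to 1.1 mmHg from -5. That is further than LOCF in 12 of 16 comparisons (all 8 with R = 15, 4 of 8 with R = 8).

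If the true week-24 effect is zero, LOCF at 160 shows -1.11 to -0.43 and measured values show +0.36 to +1.09.

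**The case against.** **The team already plans to collect data from patients who leave.** This stands in part, and is why the point says readings *may* be replaced. But that sentence names patients who quit or miss a visit, not those whom the protocol removes. A reader might infer that the data are certainly lost; the text does not go that far.

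**The threshold and post-withdrawal follow-up may sit in the full protocol or the operating procedures.** True, so the missing threshold is not itself criticised. The point concerns what the article does state: withdrawal from the trial.

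**LOCF is closer to -5 than the proposed alternative.** At week 24 and 160 this is mostly correct. A reader might set LOCF against measured follow-up and attribute the whole gap, 0.6 to 1.7 mmHg, to the withdrawal rule. That is not supported. In the largest case LOCF's own departure is 0.6 and the other 1.1 is the assumed rescue effect. Measured values estimate something different: the effect under a policy that includes rescue.

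**It is too late to change.** Partly right. Trial status reports 30 patients randomised, but expects follow-up to end in October 2020. Counting 36 weeks back from 31 October 2020 puts the last randomisation at about 22 February 2020 and the last week-12 visit at about 16 May, before publication on 22 June 2020.

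**Conclusion.** The point holds as a minor one. The rule as written can remove SBP readings for a reason tied to the outcome, and LOCF then supplies stale or selected values. The clearest exposure is at weeks 24 and 36, where LOCF's distortion is about 0.3 to 0.6 mmHg at a threshold of 160, up to 0.4 at 170 and up to 0.13 at 180, exaggerating a persisting effect. Week 12 is pulled towards zero only when baseline is carried forward, by up to 1.0, 0.4 and 0.13 mmHg. It is about unbiased when a trial reading is carried and untouched when the event is found at the week-12 visit.

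A reader might infer that the primary result is seriously biased. The documents do not support that: every shift is below the standard error of about 2.8 to 3.6 mmHg, and which detection case applies is unknown. All sizes rest on assumed means, SDs, correlations and thresholds. Confidence is medium.

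**What to change.** Replace the withdrawal clause in Adverse events with wording such as: *the study intervention may be stopped and the patient treated as clinically needed; unless consent is withdrawn, the patient stays in follow-up for SBP at the remaining planned visits and for safety.* Exempt these patients from the instruction in Interventions not to change drugs. Use the measured values in the ITT analysis, and report these events and rescue medication by arm.

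**Cost.** One amended sentence and one exception. No visits are added. Already planned visits are kept for roughly 5 to 15 of 60 patients at 160, 1 to 5 at 170 and about 1 or fewer at 180, under the same assumptions (trigger at mid-period or week 12, half to all events detected).

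**Downside.** The result is a treatment-policy estimate diluted by rescue, so it will not generally lie closer to the no-rescue effect. What is gained is real, unselected readings and continued safety follow-up. This suits the planned larger trial, which the Discussion says will assess effectiveness in the real world. In this pilot the change may reach only the remaining week-24 and week-36 visits; its main use is in the larger trial.

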### Quality control

The program has been reviewed and revised by clinical acupuncturists and statisticians. Prescribed standard operating procedures are screening of patients, blood pressure monitoring, therapeutic criteria, random methods, and acupoint stimulation, and the case report form (CRF) will be filled in. The CRF will be completed on paper copies and then entered into the Excel spreadsheet to ensure the accuracy of the data. All modifications of the data can be traced through the CRF. The ethics committee of Beijing University of Chinese medicine will audit trial conduct per 12 months.

### Sample size

This is a pilot trial, and the sample size is based on the minimum sample size of clinical trials. Each group will include 30 participants, a total of 60 participants. This is the minimum number of participants used for comparative analysis to determine the initial data of main outcome measurements and explore for future large-scale randomized controlled trial [30].

### Statistical analysis

Statistical analysis will be conducted by SPSS version 23.0 (IBM SPSS Statistics, NY, USA). Intention-to-treat analysis (ITT) will be applied to all cases randomly assigned to each group [31]. We will try our best to collect the data for the patients who quit or lost the visit in this trial. The last observation carried forward (LOCF) will be used for missing data. There is no interim analysis or additional analysis in this trial. The level of significance will be established at *α* < 0.05 with a two-sided test. Patients’ baseline characteristics will be described for the two groups. Continuously distributed variables will be described using mean ± standard deviation (M ± SD) or median and quartile intervals. Discrete variables will be described by frequencies and percentages. For the primary outcome, the change in SBP between baseline and 12 weeks after treatment will be calculated and the difference of the change in SBP between the two groups will be tested using Student’s *t* test or the Wilcoxon rank sum test. For secondary outcomes, Student’s *t* test, chi-squared test, Fisher’s exact test, or the Wilcoxon rank sum test will be used to test the difference of the outcomes including the DBP, BMI, IPAQ, and SF-12, between groups according to the distribution of variables.

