In this study, we hypothesize that TEAS has an additional antihypertensive effect on stage 1 hypertension patients after lifestyle interventions. The results derived from this study will be used to explore the efficacy and safety of TEAS in lowering BP and calculated the appropriate sample size for a future large clinical trial.

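### LOCF turns a missing week-12 SBP into a change of exactly 0 mmHg, so the primary treatment difference depends on how many and which patients drop out of each arm

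*Protocol article*

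**What the plan says.** - Primary outcome (Outcomes section): "The primary outcome of the study is the change in mean SBP between baseline and 12 weeks after treatment". The abstract also gives baseline to 12 weeks.
- Other SBP times (Secondary outcomes): "The mean SBP will be evaluated at weeks 24 and 36 after randomization". DBP, taken by the same method, and the other secondary outcomes "will be evaluated at baseline, 12 weeks, 24 weeks, and 36 weeks".
- Analysis set (Statistical analysis): "Intention-to-treat analysis (ITT) will be applied to all cases randomly assigned to each group".
- Missing data (same section): "The last observation carried forward (LOCF) will be used for missing data". The sentence just before it promises an effort to obtain data from patients who leave or miss a visit.
- Further analyses (same section): "There is no interim analysis or additional analysis in this trial".
- Use of the pilot: the Background lists among the purposes of the results "calculated the appropriate sample size for a future large clinical trial", and the abstract says the same in substance.
- Adverse events: a patient with uncontrolled hypertension is withdrawn.
- Retention: adherence calls and messages (Discussion) and the gift of the device on completion (TEAS section) are described for the TEAS group only.

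**The concern.** LOCF needs an earlier post-baseline value to carry. By the visits in the text there is none before week 12, so for the primary outcome the rule is baseline carried forward and the imputed change is 0 mmHg.

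That value is not neutral. Both arms receive lifestyle education, which the Discussion regards as needed for lowering pressure in mild hypertension. Patients also qualify on a raised reading at screening, so some regression to the mean is likely. A zero therefore understates the fall expected in a typical dropout. In a patient withdrawn for uncontrolled hypertension it does the opposite, recording a worsening as no change.

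The reminders and the device gift may retain more TEAS than control patients, while a burdensome home treatment could work the other way. The direction of the bias cannot be settled in advance, so LOCF cannot be defended as conservative.

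At weeks 24 and 36 the rule carries the end-of-treatment value into the period after the 12-week course. Persistence of the effect is then assumed where it should be measured.

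At stake are the primary comparison and the estimates the pilot is meant to hand to the next trial.

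**Working it through.** **The plan's own figure.** The sample size is 30 per arm, 60 in total, set as a pilot minimum. The protocol gives no effect size, SD, power or dropout rate, so there is no power calculation to reproduce.

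**Inputs.** From the protocol: 30 per arm, two-sided 5% test, two-sample comparison of change scores. Assumed here: mean changes, SD 12 mmHg unless stated, dropout rates, and 80% power for the next trial.

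**Formulas.** Let a share d of an arm be imputed as 0, and let the full arm have mean change m and SD s, with dropout unrelated to outcome.
- Arm mean = (1 - d)m
- Arm variance = (1 - d)s² + d(1 - d)m²
- LOCF difference = (1 - dT)mT - (1 - dC)mC

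**1. No true effect, both arms -6 mmHg (dropout TEAS/control).**
- 5%/20%: (0.95)(-6) - (0.80)(-6) = -5.7 + 4.8 = -0.9
- 0%/25%: -6.0 + 4.5 = -1.5
- 20%/5%: -4.8 + 5.7 = +0.9

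Simulated type I error (t test, 30 per arm, SD 12, 40,000 runs): with 10%/30% dropout, about 6% if both arms fall 5 mmHg and about 9% if both fall 10. With 20%/20% it is 4.5% and 3.6%, so the test is then conservative.

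**2. True difference -5 mmHg (TEAS -10, control -5, SD 12).** Next-trial size per arm is n = 2(1.960 + 0.842)²s²/δ² = 15.70 s²/δ². With the true values, 15.70 × 144/25 = 90.4, so 91.

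| Dropout TEAS/control | LOCF difference | Pooled SD | n, target fixed at 5 | n, LOCF difference as target |
|---|---|---|---|---|
| none | -5.0 | 12.0 | 91 | 91 |
| 20%/20% | -4.0 | 11.2 | 79 | 123 |
| 10%/30% | -5.5 | 11.1 | 77 | 64 |
| 30%/10% | -2.5 | 11.3 | 80 | 319 |
| 0%/20% | -6.0 | 11.5 | 83 | 58 |
| 20%/0% | -3.0 | 11.7 | 87 | 241 |

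For 20%/20%, the arm variances are 0.8 × 144 + 0.16 × 100 = 131.2 and 0.8 × 144 + 0.16 × 25 = 119.2. Their mean is 125.2, or 0.87 of 144. The squared difference falls to 16/25 = 0.64. If both inputs come from the pilot, n scales by 0.87/0.64 = 1.36.

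**3. When is the SD too small?** The LOCF variance is below s² exactly when |m| < s/√(1 - d).
- m = -6, s = 12, d = 20%: 0.8 × 144 + 0.16 × 36 = 121.0, SD 11.0, variance ratio 0.84.
- Threshold for s = 10: 10.5, 11.2 and 12.0 mmHg at 10%, 20% and 30% dropout.
- Beyond it the sign reverses: s = 10, m = -15, d = 20% gives 80 + 0.16 × 225 = 116, SD 10.8.

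Within mean changes up to 10 mmHg and SDs of 10 to 15, the SD was too small in every case computed.

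**4. Outcome-related withdrawal.** If the 20% of patients with the highest changes in each arm are set to 0 (true changes -10 and -5, SD 12), the difference moves from -5 to about -4.0. The SDs fall to about 10.0 (TEAS) and 9.0 (control).

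**The case against.** Several objections have force.

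- **Retrieval.** LOCF applies only to what is still missing after the effort to collect data. This may make the problem smaller, but it does not mend the rule for the remainder.
- **Size.** With 30 per arm and SD 12, the standard error of the difference is 12 × √(2/30) = 3.1 mmHg, so a 0.9 mmHg bias is about 0.3 standard errors. In an open-label pilot that is moderate, and equal dropout makes the test conservative. This stands and bears on severity.
- **Schedule.** The text is consistent on visits, but Fig. 3 was not available, and Quality control mentions a procedure for blood pressure monitoring. A reader might infer that no reading at all exists before week 12. The documents support only that the text schedules none.
- **Further analyses.** A reader might take "There is no interim analysis or additional analysis in this trial" as a ban on sensitivity analyses. It may mean only extra outcomes or subgroups, and any separate analysis plan was not seen. As worded, though, it provides for none.
- **SD and sample size.** A reader might infer that LOCF must make the SD too small and the next trial about 16% too small (variance ratio 0.84). The first part depends on the threshold in step 3. The second needs a target difference fixed from outside. The protocol does not say which pilot quantities will size the next trial, and with the LOCF difference as target, equal 20% dropout makes n about 36% too large.

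**Conclusion.** The point holds in this form: the stated missing-data rule, applied to the visits in the text, imputes a change of 0 mmHg for every unretrieved week-12 SBP, and the primary difference then depends on dropout in each arm. Unequal and outcome-related dropout can both be foreseen from the protocol's own provisions.

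Under the assumptions shown, the distortion is about 1 to 1.5 mmHg when there is no true effect. A true -5 mmHg can appear as anything from -2.5 to -6.0. The SD of change will usually be too small, but not always. The next trial's size could come out at 58 to 319 per arm against 91, depending on dropout and on whether the LOCF difference is used as the target; no single direction can be claimed.

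These sizes rest on assumed changes, SDs and dropout rates, because the protocol states none. The rule should be fixed. Given the pilot setting and a bias that is modest against the standard error, it is not disqualifying.

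**What to change.** 1. Delete LOCF. Analyse observed SBP with adjustment for baseline, with the week-12 contrast as primary, in one of two ways:
   - a longitudinal mixed model over weeks 12, 24 and 36 that includes baseline SBP as one of the outcomes. If baseline is only a covariate, patients with no post-baseline SBP supply no information and are in effect dropped; or
   - ANCOVA on week-12 SBP with multiple imputation.
2. Add one sensitivity analysis, delta-adjusted or control-based multiple imputation, for patients with no post-baseline SBP, including those withdrawn for uncontrolled hypertension. Their outcomes are unlikely to be missing at random, and the main model cannot test that.
3. Amend the sentence on additional analyses so that this one is allowed.
4. Take both the SD and the difference for the next trial from this analysis, not from LOCF-filled data, and report the number missing at week 12 by arm.

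The cost is a rewritten paragraph, a little programming and possibly slightly wider confidence intervals. No visit or measurement changes. Trial status reports 30 of the 60 patients randomised, so the change could be made before the final analysis.

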### Randomization and masking

Eligible patients will be randomly assigned to the TEAS group or control group in a ratio of 1:1. The randomization sequence will be generated with the software SAS 9.3 by an independent statistician ([name], Beijing University of Chinese Medicine, China) using block randomization. Randomization sequence will be stored by a non-involved investigator. When an eligible patient needs to be randomized, the clinical research coordinator will contact the non-involved investigator by phone to obtain random number and assign him/her to one group. The design is open label, but the outcome assessors and statisticians who are blinded to group allocation will be responsible for collecting and analyzing the data, respectively.

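### The primary SBP comparison is valid but ignores baseline SBP; adjusting for it would remove the effect of chance imbalance and usually gain precision, at almost no cost

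*Protocol article*

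**What the plan says.** The Primary outcome section of the protocol article defines the endpoint: "The primary outcome of the study is the change in mean SBP between baseline and 12 weeks after treatment". The Statistical analysis section carries this through. Each patient's change is derived first, and the section then says that "the difference of the change in SBP between the two groups will be tested using" one of two unadjusted methods, a t test or its rank-based counterpart (Wilcoxon). No covariate is named. Baseline characteristics are to be described by group but enter no model. The same section sets the level at "0.05 with a two-sided test" and rules out anything further: "There is no interim analysis or additional analysis in this trial".

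On design, Randomization and masking says: "Eligible patients will be randomly assigned to the TEAS group or control group in a ratio of 1:1". It specifies blocks and mentions no stratification by SBP. The Sample size section says: "Each group will include 30 participants, a total of 60 participants". The Inclusion criteria admit patients on SBP of 140 to 159 mmHg, DBP of 90 to 99 mmHg, or both.

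**The concern.** A change score adjusts for baseline by subtracting it in full. That is right only if week-12 SBP rises by 1 mmHg for each 1 mmHg of baseline SBP. Patients here are enrolled on a raised reading, so some of the baseline variation is transient and the true slope may well be below 1. If the arms then differ at baseline by chance, the change score favours the arm that started higher. Thirty per arm is small enough for such differences to matter, and nothing in the stated randomization limits them.

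At stake are the precision of the one planned primary comparison and how far its estimate reflects the draw of patients. The abstract's Discussion says this pilot will inform the sample size of the next trial, so the estimate will be used again.

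This is not simply a detail left to a fuller document. The article names the primary test and excludes further analyses.

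**Working it through.** **The plan's own figure.** 30 × 2 = 60 agrees. The article gives no target difference, SD, power or dropout rate ("the sample size is based on the minimum sample size of clinical trials"), so there is nothing further to reproduce.

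**Inputs.** From the article: 30 per arm, 1:1, comparison of raw change. Assumed, because the article gives none: week-12 SD s1 = 12 mmHg; correlation r between baseline and week 12 of 0.3, 0.5 and 0.7; baseline SD s0 of 5.5, 8, 10 and 12 mmHg. The value 5.5 is what an even spread over 140 to 159 would give (19/√12 = 5.5). The true spread is uncertain, because a patient can qualify on DBP with SBP outside that window.

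**Formulas.**
- Change-score variance per patient: s0² + s1² − 2·r·s0·s1
- ANCOVA variance per patient: s1²(1 − r²)
- Slope of week 12 on baseline: b = r·s1/s0
- Standard error of the baseline difference: s0·√(2/30). Its 95% limit is 1.96 times this; its average absolute size is √(2/π) = 0.80 times this.
- Shift of the change-score estimate: (1 − b) × imbalance. Positive means towards the arm that started higher.

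Example, s0 = 10 and r = 0.3: change-score variance 100 + 144 − 72 = 172; ANCOVA variance 144 × 0.91 = 131; ratio 0.76. Here b = 0.36 and the 95% limit is 1.96 × 10 × √(2/30) = 5.06, so the shift is 0.64 × 5.06 = 3.2 mmHg.

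**Results (entries separated by slashes are for r = 0.3 / 0.5 / 0.7).**

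| Baseline SD | Variance ratio, ANCOVA/change | 1 − b | Average absolute imbalance | 95% limit | Shift at 95% limit (mmHg) |
|---|---|---|---|---|---|
| 5.5 | 0.97 / 1.00 / 0.90 | 0.35 / −0.09 / −0.53 | 1.1 | 2.8 | 1.0 / −0.3 / −1.5 |
| 8 | 0.87 / 0.96 / 1.00 | 0.55 / 0.25 / −0.05 | 1.6 | 4.0 | 2.2 / 1.0 / −0.2 |
| 10 | 0.76 / 0.87 / 0.97 | 0.64 / 0.40 / 0.16 | 2.1 | 5.1 | 3.2 / 2.0 / 0.8 |
| 12 | 0.65 / 0.75 / 0.85 | 0.70 / 0.50 / 0.30 | 2.5 | 6.1 | 4.3 / 3.0 / 1.8 |

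For scale, the standard error of the change-score effect, √(variance × 2/30), is 2.2 to 3.4 mmHg at baseline SD 8 to 10. Estimating the slope from 60 patients adds about 2% to the ANCOVA variance (1 + 1/56). ANCOVA is therefore marginally less precise where the ratio is 1.00.

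**Simulation.** 20,000 trials, 30 per arm, both SDs 10, r = 0.5, true effect −6 mmHg:
- Mean estimate: −6.01 (change score), −6.03 (ANCOVA).
- Movement per mmHg of baseline imbalance: −0.49 (change score), 0.01 (ANCOVA).
- Standard error: 2.57 against 2.26, a variance ratio of 0.78.
- Power: 63% against 75%.

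**The case against.** The strongest reply is that nothing here is invalid. Under 1:1 randomization the t test on change keeps its type I error and is unbiased on average, as the simulated means confirm. This is also a pilot, and an unadjusted difference with its SD of change is a conventional product of one. All of that stands.

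Four stronger readings might be inferred, and the documents do not support them.

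- **That regression to the mean biases the result.** It acts on both arms equally in expectation. It reaches the estimate only through chance imbalance.
- **That imbalances of 4 to 5 mmHg are to be expected.** Those are 95% limits at baseline SD 8 and 10; the average is 1.6 to 2.1 mmHg.
- **That the change score always over-corrects.** Where selection narrows the baseline SD, b can exceed 1 and the change score under-corrects, as the negative entries in the table show.
- **That the open choice between t test and Wilcoxon is itself a defect.** The rule for choosing is largely something an article may leave to the full plan.

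It is also true that no SD or correlation is documented, so the size of the gain cannot be fixed. What the reply does not answer is why a value already collected on every patient should go unused in the primary comparison.

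**Conclusion.** The point holds as a nearly free improvement, not as an error of validity. That the primary comparison is unadjusted, with further analysis excluded, is certain from the text. The size of the benefit is not.

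With week-12 SD 12 and r of 0.3 to 0.7, the variance ratio is 0.65 to 0.85 at baseline SD 12, 0.76 to 0.97 at SD 10, 0.87 to 1.00 at SD 8 and 0.90 to 1.00 at SD 5.5, each before the 2% for estimating the slope. The gain therefore runs from about a third of the variance to nothing. For baseline SD 5.5 to 10, the shift at the 95% limit of imbalance runs from −1.5 to +3.2 mmHg. The upper end is about one standard error of the effect (3.4 mmHg in that cell); the shift at an average imbalance is well under half as large.

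The case covers baseline SBP in the primary analysis only. Nothing was computed that would support further covariates or the same change for the secondary outcomes.

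**What to change.** In Statistical analysis, make the primary analysis an ANCOVA of week-12 SBP (or, equivalently for the group effect, SBP change) on group with baseline SBP as covariate. Report the adjusted mean difference with its 95% CI. Keep the unadjusted t test or Wilcoxon test as a supportive analysis, and amend the sentence that excludes additional analysis so that it permits this.

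The cost is one degree of freedom and a change of wording; no new data are needed. The change should be made and dated before unblinding. The article's Trial status section reports 30 patients randomized and follow-up expected to end in October 2020, and Randomization and masking says the statisticians are blinded, so as of the article this was possible. If the data have since been unblinded, the adjusted analysis should be reported as not pre-specified.
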